#### **8.5.1.4 Physical examination**

At the Visits paediatricians will perform a physical examination. It will be determined if findings are normal or remarkable. The following will be covered:

- General appearance
- Skin
- Fontanel
- Ear/Nose/Throat
- Lymphoid nodules
- Heart
- Pulmo
- Abdomen
- Extremities
- CNS
- Others
- Medications necessary

The paediatrician will also ask for side effects or any adverse effects or unwanted incidences. If the child is sick, diagnosis will be recorded as well as a comment / remark of the paediatrician.

#### **8.5.1.5 Blood withdrawal**

In the context of blood sampling following aspects will be reported:

- Child fasted (last feeding at least 2 hours ago)
- Time of last feeding (hours)

- Amount of last feeding: complete meal / minor amounts
- Blood samples taken
- Enough blood taken
- Blood analyses results

Blood count analysis result must be filled in the CRF after completed analysis. Original reports must be attached after last page of the CRF.

Results from Munich (amino acid profiling, fatty acid profiling) will be reported in one table for all subjects. This list will be attached to the file where CRF are stored after completion of analyses.

#### **8.5.1.6 Present feeding**

The paediatrician will ask for present feeding as:

- Fully breastfeeding
- Partially breastfeeding
- Fully formula-feeding

According to the answer given by the parents / caregivers the paediatrician has to decide how to go on with the Visit. In case of fully formula-feeding and partially breast-feeding (potentially skipping breastfeeding) the child will be randomised.

#### **8.5.1.7 Randomisation**

If the present feeding is fully formula-feeding or partially breast-feeding (potentially skipping breastfeeding), the Visit can go on with Randomisation (chapter 8.4, chapter 9.6). Infants will be assigned to a Formula Random Number.

#### **8.5.1.8 Formula accountability**

Parents / caregiver will receive instructions on how to prepare the formula, two covering boxes with formula with their specific Formula Random Number and an envelope also labelled with the assigned Formula Random Number containing light blue spoons, to be used for preparation of the formula.

Hand out of formula and spoons must be documented in the Formula Accountability Form (FAF). The parents / caregivers will be told to bring back empty formula boxes at every visit.

#### **8.5.1.9 Reminder (Diary)**

Parents of randomised infants and parents of infants who are fully breastfed will receive the Diary 1 with the corresponding Subject ID Number and are asked to bring it back to the next Visit. Instructions on how to fill it out correctly are given on the diary. Diaries for the breast

feeding group and the formula feeding group differ slightly. The investigator needs to be aware of the two different types of diaries (Appendix 15.13).

#### **8.5.1.10 Reminder (Visit)**

At the end of the Visit an appointment for the next Visit will be made and the Investigator has to sign the CRF.

### **8.5.2 Visit 1 (Day 30±2), Visit 2 (Day 60±3) and Visit 3 (Day 90±3)**

Visit 1, Visit 2 and Visit 3 will each be conducted in an equal manner as set out below. The Subjects ID Number and date of Visit must be reported on the CRFs. Anthropometric data will be assessed and a physical examination will be performed as described in chapter 8.5.1.3 and 8.5.1.4. At each Visit the Investigator n must check whether a case of “Withdrawal” is apparent or not. Is that the case the Investigator needs to complete the “Withdrawal sheet” at the end of the CRF.

#### **8.5.2.1 Health observations**

In addition any health observation observed during the period between the visits will be thoroughly documented on the CRF and if necessary documented in the respective form (e.g. AE).

#### **8.5.2.2 Compliance to protocol**

The compliance of subjects to the protocol will be checked according to following questions:

- Only assigned formula was given?
- Fully breastfeeding
- Fully formula-feeding
  - At Visit 1 only: if YES – indicate the date when for the first time fully formula-fed
- Liquid intake
- Complementary feeding

#### **8.5.2.3 Formula associated observations**

The paediatrician will ask for formula acceptance and formula handling.

**8.5.2.4 Adverse / Serious adverse events**

Adverse events (AE) and serious adverse events (SAE) must be well documented. AE needs to be documented in the “Non-serious AE” form attached to the CRF. SAE documentation and report need to follow another procedure (separate SAE form). The definition and handling of AE and SAE is described in chapter 10 .

**8.5.2.5 Formula accountability**

Subject of the control and study group will receive new study formula with their specific Random Number (Visit 1 and Visit 3: one covering box; Visit 2: two covering boxes and a numbered envelope with spoons). Hand out of formula and spoons must be documented in the Formula Accountability Form (FAF).

**8.5.2.6 Reminder (Dairy)**

Subjects will receive the next diary. Subjects of the reference group will receive the Diary (type “breast feeding”). The last Diary will be discussed with the paediatrician and missing details will be discussed and if necessary and possible completed.

**8.5.2.7 Reminder (Visit)**

At the end of the Visit an appointment for the next Visit will be made and the Investigator has to sign the CRF

**8.5.3 Visit 4 (Day 120 ± 3)**

Visit 4 will be performed similar to Baseline Visit with assessment of anthropometric data, a physical examination and blood withdrawal, but without core data assessment.

Like on the other Visits compliance to protocol will be assessed and formula associated observations reported. Adverse and Serious adverse events have to be documented as set out in Chapter 8.5.2.4.

The paediatrician has to discuss the last Diary 4 with the parents / caregivers.

**8.5.3.1 Study termination**

All subjects, who had been enrolled in the study according to inclusion and exclusion criteria and who took part in the study according to study protocol, will terminate the study regularly with the last Visit at the age of 120 ± 3 days (Visit 4). The study will be terminated when the last subject completed the last visit (“last subject out”). Not later than 90 days after termination of the study the ethical committee (EC) must be informed about study termination by the

Principal investigator. Not later than 1 year after study termination the principal investigator will provide a final study report to the EC if desired by the EC.

The paediatrician has to document if:

- the subject took part in the study successfully in accordance with the study protocol
  - if NO: the PI must check if a protocol violation was given and needs to complete the protocol violation/deviation form
- all of the formula boxes (empty and unused ones) are given back

Information about complementary feeding will be handed out to the parents together with a selection of baby products.

## **8.6 Diaries**

Three days before each Visit (except Baseline Visit) parents / caregivers are asked to fill out a diary at home. Diaries for the formulae groups and the reference breastfeeding group differ slightly (Appendix 15.13).

Parents / caregivers of the formulae groups are asked to write down bottle feeding, concomitant diet and tolerance as defined in chapter 7.3.1. Parents / caregivers of the breastfeeding group are asked to write down number of breast meals, concomitant diet and tolerance.

Diaries will be brought back to the paediatrician at the next study Visit. It will be checked for correct filling out and if necessary entries will be discussed.

## **8.7 Reminder call**

Between the Visits, parents / caregivers will be called by the study team at Day 15 ( $\pm 3$ ), Day 45 ( $\pm 3$ ), Day 75 ( $\pm 3$ ) and Day 105 ( $\pm 3$ ).

Following measures will be assessed and documented on the “protocol of the reminder call” (Appendix 15.14):

- Compliance to protocol (Type of feeding, Formula shift completed – if YES: first day of completely bottle feeding (Call 1 only), liquid intake, complementary feeding)
- Formula associated observations (acceptance, handling)
- Reminder (next visit, filling out the diary, empty formula boxes etc.)

If a member of the reference breast feeding group is called, non applicable questions/answers will be marked with NA (=not applicable) by the investigator on the protocol of the reminder call.

## 8.8 Biological samples

### 8.8.1 Responsibilities, parameters and methods

Following parameters will be assessed at study site in Belgrade:

For health evaluation of each subject:

- Full blood count with differential
- C-reactive protein (marker of acute infections)
- Astrup (marker for respiratory status)
- Electrolytes Na, K, Cl (electrolyte metabolism)
- Glucose
- Total bilirubin (Baseline Visit only)

For protein status assessment and estimation of metabolic burden caused by protein intake:

- Serum albumine
- Serum creatinine
- Blood urea nitrogen

Blood count will be analyzed by routine laboratory methods in clinical laboratory with Olympus analyzer. The same Olympus analyzer will be used for protein status measurements according to instruction manuals provided by Olympus GmbH, which are filled in the Trial Master File and Investigator Site File.

The group of [name]. [name] will conduct metabolome analysis including:

- plasma amino acid profile (protein status) by Liquid Chromatography-Tandem Mass Spectrometry (description in Appendix 15.15)
- plasma phospholipid fatty acid profile (metabolic status) by Gas chromatographic analysis with an Agilent 5890 II gas chromatograph (description Appendix 15.16)

In total an amount of ~4.7 ml of whole blood needs to be drawn at Baseline Visit and Visit 4 each. As back-up for metabolome analysis last blood drops from the plain needle will be collected on a filter card. Analyses regarding nucleic acids (DNA, RNA) will not be conducted with the samples obtained in the context of the BeMIM study.

The Principal Investigator will receive all analyses results to include them at the end of the CRF.

### 8.8.2 Collection and preparation

Some of the material for sample collection will be provided by the group of [name]. [name], Dr. von Hauner Children's Hospital, Munich. A list of this material is added below (Appendix 15.17).

#### 8.8.2.1 Time of sample collection

As far as possible, fasted blood samples should be collected - that means at Baseline Visit soonest 2 hours after the last feeding, at Visit 4 soonest 3 hours after the last feeding. Time (hours ago) of last feeding as well as amount of the last meal (complete meal or minor amount) must be reported.

#### 8.8.2.2 Procedure of blood sampling

Blood will be drawn off only in agreement with the parents / caregivers (part of IC). The paediatrician is responsible for this. Pricking two times is considered as being ethical – but more than two times is not allowed. Procedure of blood sampling does not differ between Baseline Visit and Visit 4.

Preparation: Mark material for each subject identically (label will be provided by the LMU team) so that identification can be done easily:

[figure not shown]

Volumes: A total of ~4.7 ml blood from a peripheral vein must be collected.

- *for analyses done in Belgrade:* a minimum of 2 ml blood must be collected in a standard tube(s)
- *for analysis done in Munich:* a minimum of 2.5 ml blood from a peripheral vein must be collected into an opened 2.7 ml S-Monovette (containing potassium-EDTA as clotting inhibitor) and on a filter card using a plain needle (see Appendix 15.18).

Procedure of blood sampling:

- unscrew the cap of the *S-Monovette*
- remove the syringe plunger of the *S-Monovette* by moving it backwards until it snaps in and break it by moving it to the side
- use a plain needle to let the infant's blood drop into the *S-Monovette*
- close the *S-Monovette* with the screw cap
- drop blood from the needle on the provided filter card to fill one circle completely for back-up of metabolome analyses.

Immediate further handling of blood samples:*For analysis done in Belgrade*

- Transfer the vial for blood count analysis as soon as possible to clinical laboratory
- Protein status measurement:
  - transfer the vial as soon as possible to the laboratory for separation of cells and plasma by centrifugation. Store the vial at room temperature until centrifugation. Time under room temperature should not exceed 60 min.
  - Centrifuge for 10 min at room temperature (20°C) with 2000 x g.

*For analysis done in Munich (see SOP in Appendix 15.18)*

- Shake the *S-Monovette* – gently, but thoroughly – immediately after finishing blood collection.
- Transfer the filled *S-Monovette* as soon as possible to the laboratory for separation of cells and plasma by centrifugation. Time at room temperature before centrifugation must not exceed 60 min.
- Centrifuge for 10 min at room temperature (20°C) with 2000 x g.
- Transfer the plasma into a *Nunc 1 ml CryoTube* (see Appendix 15.17).

**The final volume of plasma samples from infants must be 1.0 ml minimum!**

- Label and store *Nunc 1 ml CryoTube* with plasma at -20°C.
- After removal of plasma and labeling, freeze the *S-Monovette* with the cells in an upright position at -20°C.
- After labeling, allow the *filter card* to dry at air for at least 4 hours. Then put it in the *plastic bag* and freeze at -20°C.

### 8.8.3 Logistics

Plasma samples, frozen erythrocytes and filter cards for Munich will be collected and stored in a refrigerator at -20°C. The shipment to Munich will take place in regular intervals. Samples will be sent by express (DHL or Federal express) in isolated boxes on ~10 kg dry ice.

The study team in Belgrade is asked to inform members of [name]. [name] laboratory by telephone, Email or fax prior to shipment. Shipment should take place always on Mondays.

### 8.8.4 Reporting of results

Some free space is provided in the CRF of Baseline Visit and Visit 4 to fill in the results after complete blood analyses. Original reports must be attached after last page of the CRF. Results from Munich (amino acid profiling, fatty acid profiling) will be provided in a tabular form

comprising results of all infants. A copy of this comprehensive table will be attached in addition to the collected CRF's at the end of the study.

### **8.9 Breaking the code**

The investigator will receive a set of sealed envelopes containing product identification.

The envelopes may be used in circumstances when the investigator identifies an urgent need to break the code. In such cases the rationale must be documented on the corresponding envelope, with immediate notification of the monitor.

The code break will also be reported in the CRF and events leading to the emergency breaking will be recorded in the serious adverse events report form. Code Break must also be documented in the protocol violation form (Appendix 15.22) as this is defined as a protocol violation.

### **8.10 Data management**

#### **8.10.1 Data on CRFs**

All collected subject data will be recorded in compliance with GCP standard in Case Report Forms (CRF) (Appendix 15.12). Data of laboratory analysis done at site and at the von Hauner Children's Hospital, Munich will be entered as soon as results are obtained.

Site must complete the CRF in a timely manner and the investigator must promptly review and sign the completed CRFs for each subject. The Principal Investigator is responsible for quality, consistency and completeness of the CRF data.

The original CRFs will be collected by the Monitor and provided to the Sponsor. The Principal Investigator as well as the Monitor will receive a copy. All case report forms (CRFs) will be kept secret and stored for ten years by the Sponsor. Data protection will be guaranteed.

#### **8.10.2 Computerized data entry**

Primarily responsible for data entry is the team of the Chief Investigator (LMU). At site (Clinic in Belgrade) data will be entered by [name] from the CRFs into a computer database (Microsoft, Excel). Data entry will be verified by the study monitor (LMU). Evaluation of the data will be done by the Statistician at the von Hauner Children's Hospital, Munich using Stata® Data analysis and statistical software.

#### **8.10.3 Organization of data sheets**

Tab. 1 overviews how storage of all data sheets involved in this study will be handled. The team in Belgrade is responsible to organize distribution of most of the data sheets to the

sponsor (e.g. via the monitor) and the monitor. The sponsor and the monitor must store the data sheets in the corresponding files.

| DOCUMENTS                                | Responsible | ORIGINAL |         | CARBON   |          | COPY     |          |
|------------------------------------------|-------------|----------|---------|----------|----------|----------|----------|
|                                          |             | Given to | File in | Given to | File in  | Given to | File in  |
| Informed consent                         | PI          | PI       | ISF     | SUB      |          |          |          |
| CRF                                      | PI          | S        | TMF     | PI
M  | ISF
- |          |          |
| Diary                                    | PI          | PI       | ISF     |          |          | S
M   | TMF
- |
| Reminder call                            | PI          | PI       | ISF     | M        | -        | S        | TMF      |
| Subject screening list                   | PI          | PI       | ISF     |          |          | S        | TMF      |
| Subject identification list              | PI          | PI       | ISF     |          |          |          |          |
| Subject randomisation list               | PI          | PI       | ISF     |          |          | S
M   | TMF
- |
| Serious adverse events                   | PI          | PI       | ISF     |          |          | S
M   | TMF
- |
| Study Formula Inventory Form             | PI          | PI       | ISF     |          |          | S        | TMF      |
| Monitoring reports                       | M           | S        | TMF     |          |          | PI*      | ISF      |
| Report of laboratory analysis (LMU)      | M           | M        | -       |          |          | S        | TMF      |
| Report of laboratory analysis (Belgrade) | PI          | PI       | ISF     |          |          | S
M   | TMF
- |
| Final study report                       | M
PI     | M
PI  | -
-  | S        | -        |          |          |

**Tab. 1: Overview of data-sheet organization**

#### Abbreviations

PI: Principal Investigator / Belgrade:

ISF: Investigator site file / Belgrade

SUB: Subject

M: Monitor / LMU:

S: Sponsor / Pfaffenhofen:

TMF: Trial master file / Pfaffenhofen

\*: Principal investigator receives follow up letters during the study.

#### 8.10.4 Unblinding procedure

After the last subject completed the study, all analyses are done and all data are entered from the CRF's into the computer data base, data will be checked for completeness and plausibility. Last step before statistical analyses will be the unblinding of the Randomisation code. Information of the Randomisation Code will be provided by the Sponsor to the Chief Investigator and Principal Investigator Teams after the data base is locked.

## 9 Statistical methods and data analysis

### 9.1 Statistical background

The study is proposed to show the non-inferiority of an infant formula with reduced protein content (1.89 g/100 kcal) in comparison to a standard infant formula (2.2 g protein /100 kcal). Primarily weight gain in g/day will be assessed.

Statistics include detailed description of all recorded data. Regarding the comparison of the two formula groups general, adequate statistic designs will be applied. Statistic analysis will be performed with the program STATA 9.2.

### 9.2 Hypothesis to be tested

$H_0$  (to be rejected): The mean daily weight gain in the intervention group (formula with reduced protein content) is more than 3 grams per day lower than in the control group (standard formula).

$H_{\text{alternative}}$ : The mean daily weight gain in the intervention group (formula with reduced protein content) is not more than 3 grams per day lower than in the control group (standard formula).

### 9.3 Primary outcome variable

The main outcome variable "weight gain" will be calculated by subtracting the weight obtained at the 4 months study visit from the Visit 1 weight divided by the days passed between those visits.

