**Primary outcome**

Weight in grams will be assessed in all clinical study Visits. Average **weight gain / d** between Visit 1 (30 ± 2 days of life) and Visit 4 (120 ± 3 days of life) is the primary outcome.

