## 7 Definition of measures

### 7.1 Primary Outcome

The primary outcome of the study is the average daily weight gain in grams (g/d) between Visit 1 (30 ± 2 days of life) and Visit 4 (120 ± 3 days of life).

The weight in grams will be assessed at each Visit by responsible study person and average daily weight gain in g/d during the study period will be calculated.

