### 9.4 Secondary outcome variables

Length gain: same calculation as for primary outcome

Gain in head circumference: same calculation as for primary outcome

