### 9.5 Sample size calculation

Based on previous publications and own data we can expect the children to grow on average 30 grams per day with a standard deviation of 6 grams between birth and 4 months of life. Growth studies should be designed to have a power to detect a difference in weight gain equal to 0.5 standard deviations according to the SCF report. Thus, one would need about 70 children in each formula group under the assumption of non-inferiority (one-sided test), a

significance level of 2.5% and a power of 85%. We expect a true loss-to follow-up of about 10-15%. Additionally, we expect that another 15% will switch formula due to preference changes which usually take place in the first months of life. These children will be only available for an intention-to-treat analysis. Thus, 100 children in each formula arm, as well as in the breastfed group will be included to have also sufficient power in a per-protocol analysis.

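### Section 9.3 writes the primary outcome formula in the wrong order, so read literally every growing infant has a negative weight gain

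*Protocol*

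**What the plan says.** Section 9.3 is the only place in the protocol that spells out how the primary outcome is computed. It does so by "subtracting the weight obtained at the 4 months study visit from the Visit 1 weight divided by the days passed between those visits".

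The other sections describe the same quantity as a gain:

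- Section 7.1: "The primary outcome of the study is the average daily weight gain in grams (g/d) between Visit 1" and Visit 4. The synopsis names the same outcome.
- Section 9.2 places the null hypothesis on the low side, where mean daily gain in the intervention group "is more than 3 grams per day lower than in the control group (standard formula"). Under the alternative it "is not more than 3 grams per day lower than in the control group".
- Section 9.5, on planning values: "we can expect the children to grow on average 30 grams per day with a standard deviation of 6 grams between birth and 4 months". The test is one-sided at 2.5%.

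Section 9.4 extends the rule to the secondary growth outcomes: "Length gain: same calculation as for primary outcome", and likewise for head circumference. Amendments 1 to 3 do not touch the formula.

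**The concern.** To subtract A from B is to form B minus A. Section 9.3 therefore defines weight gain as the Visit 1 weight minus the 4-month weight, which is negative for any infant who grows. The sentence is complete and grammatical, with its two terms in reversed order. It has a second fault: as worded, the division by days could attach to the Visit 1 weight alone rather than to the difference.

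In a two-sided comparison a reversed sign would be cosmetic. This test is one-sided with a margin on one side only, so the sign of the variable matters. What the trial has to rule out is a growth deficit on the reduced-protein formula. An operative formula for the primary endpoint should be one that a programmer can follow exactly, and this one cannot be followed as written without contradicting the rest of the protocol.

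**Working it through.** **Inputs.** Margin 3 g/d (9.2). SD 6 g/d, expected gain 30 g/d, one-sided alpha 2.5%, power 85% and about 70 evaluable infants per formula group (9.5). Visits at day 30 and day 120 (7.1), so nominally 90 days apart.

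**1. The plan's own sample size.** The margin is 0.5 SD: 0.5 × 6 = 3 g/d. With a true difference of zero,

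n per group = 2 × (1.960 + 1.036)² × 6² / 3² = 71.8, rounded up to 72.

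This agrees with the stated figure of about 70. With exactly 70 per group, SE = 6 × √(2/70) = 1.014 g/d and power = Φ(3/1.014 − 1.960) = 84.1%. The planning calculation is consistent with a positive gain variable.

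**2. What the formula returns.** Take an infant gaining 30 g/d for 90 days, a total of 2,700 g, with Visit 1 weight w.

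| Reading | Formula | Result |
|---|---|---|
| Intended | ((w + 2,700) − w) / 90 | +30 g/d |
| As written, whole difference divided | (w − (w + 2,700)) / 90 | −30 g/d |
| As written, only Visit 1 weight divided | w/90 − (w + 2,700) | below −2,700 for any w; mixed units |

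For illustration, with an assumed w of 4,200 g (not from the protocol), the last line gives 46.7 − 6,900 = −6,853, which has no meaning. Only division of the whole difference gives g/d.

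**3. Conditional effect on the test.** Let d be the true difference in gain, intervention minus control. With the intended sign,

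P(declare non-inferior) = Φ((d + 3)/1.014 − 1.960).

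If the reversed variable were entered in the 9.2 comparison and a less negative score read as a higher gain, d is replaced by −d.

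| True d (g/d) | Intended sign | Literal sign, unexamined |
|---|---|---|
| −4 | 0.16% | >99.9% |
| −3 | 2.5% | >99.9% |
| 0 | 84.1% | 84.1% |
| +3 | >99.9% | 2.5% |
| +4 | >99.9% | 0.16% |

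Worked line at d = −3: intended, Φ(0 − 1.960) = 2.5%; literal, Φ(6/1.014 − 1.960) = Φ(3.96) > 99.9%. At d = 0 the two columns coincide, so power and sample size are untouched.

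**The case against.** The best reply is that no competent reader would be misled. Section 9.3 itself calls the variable weight gain, 7.1 fixes quantity, units and interval, 9.5 expects a positive 30 g/d, and 9.2 speaks of which group gains less rather than of a signed score. An infant scoring −27 has plainly gained less than one scoring −30, so the hypothesis as worded still guards against a deficit; a sign change merely mirrors the estimate and its interval. A column of negative gains would also be noticed at once. Finally, a reader who repairs the loose division in the sentence has little reason not to repair the word order too.

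Most of this stands. A reader might infer that the planned non-inferiority test protects the wrong side. The protocol does not support that. It would take two steps: computing the reversed variable, and then treating a less negative value as a larger gain against the words of 9.2. The second step is written nowhere. Nor does anything in the protocol show that the analysis was run that way.

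What does not fall away is that a stated rule for the primary endpoint is wrong as written, is inherited by two secondary outcomes, and is not corrected elsewhere.

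**Conclusion.** The point holds as a drafting error in an operative formula, with low practical risk. Section 9.3 reverses the subtraction and is loose about the division; it disagrees with 7.1, 9.2 and 9.5, which make the intended direction clear. Sample size and power are unaffected.

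The contrast of more than 99.9% with 2.5% at a 3 g/d deficit is a conditional worst case and not an estimate of risk. It rests on 70 per group, the planning SD of 6 g/d, an unadjusted normal comparison, and an analyst who uses the reversed variable without looking at it. Section 9.2 already gives direction and margin, so the absence of a confidence-limit rule here is no defect.

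**What to change.** Replace the sentence in 9.3 with an explicit formula:

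(weight at Visit 4 − weight at Visit 1) / (days between Visit 1 and Visit 4), in g/d.

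The brackets settle both the sign and the division. Section 9.4 then inherits the right calculation for length and head circumference without further change. The cost is one sentence; design, sample size and conduct stay as they are.
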